## Abstract

**Introduction:**

Although most stroke survivors show some spontaneous neurological recovery from motor impairments of the most-affected leg, the contribution of this leg to standing balance control remains often poor. Consequently, it is unclear how spontaneous processes of neurological recovery contributes to early improvements in standing balance.

**Objective:**

We aim to investigate (1) the time course of recovery of quiet stance balance control in the first 12 weeks poststroke and (2) how clinically observed improvements of lower limb motor impairments longitudinally relate to this limb's relative contribution to balance control.

**Methods and Analysis:**

In this prospective longitudinal study, a cohort of 60 adults will be recruited within the first 3 weeks after a first-ever hemispheric stroke and mild-to-severe motor impairments. Individual recovery trajectories will be investigated by means of repeated measurements scheduled at 3, 5, 8, and 12 weeks poststroke. The Fugl-Meyer Motor Assessment and Motricity Index of the lower limb serve as clinical measures of motor impairments at the hemiplegic side. As soon as subjects are able to stand independently, bilateral posturography during quietly standing will be measured. First, the obtained center-of-pressure (COP) trajectories at each foot will be used for synchronization and contribution measures that establish (a-)symmetries between lower limbs. Second, the COP underneath both feet combined will be used to estimate overall stability. Random coefficient analyses will be used to model time-dependent changes in these measures and, subsequently, a hybrid model will be used to investigate longitudinal associations with improved motor impairments.

**Discussion:**

The current study aims to investigate how stroke survivors “re-learn” to maintain standing balance as an integral part of daily life activities. The knowledge gained through this study may contribute to recommending treatment strategies for early stroke rehabilitation targeting behavioral restitution of the most-affected leg or learning to compensate with the less-affected leg.

## Introduction

### Background

Stroke is a major cause for acquired serious disability in adults worldwide (1). It is well known that stroke affects standing balance, for example posturographic studies revealed that stroke survivors show increased body sway reflected by center-of-pressure (COP) movements (2–5). Recovering the ability to maintain standing balance is seen as a prerequisite for regaining walking independence (6), and residual deficits are associated with limited community ambulation (7, 8) and falls (9–11). Accordingly, falls remain a major problem with approximately 50 to 70% of community-dwelling stroke survivors experiencing a fall recently after being discharged home from rehabilitation facilities (9, 10, 12). As such, deficient standing balance control may contribute to chronic disability and fall-related injury resulting in greater economic costs due to the need of care (13) and poor quality of life (14).

Improving stroke rehabilitation services requires a profound understanding about the behavioral changes underlying impaired as well as improved balance control execution, together with the time windows in which they develop. This may enable clinicians to define appropriate treatment targets and rehabilitation goals early onwards. From this perspective, particularly explorative longitudinal research with repeated measurements early in time is warranted to distinguish between behavioral restitution and compensation when control of standing balance is restored (15, 16). As stroke recovery is a complex process that likely involves both spontaneous and learning-dependent mechanisms (17, 18), this research should be based on a commonly shared framework for classifying and using uniform terminology.

The WHO's international classification of function, disability and health (ICF) model may serve as such framework by categorizing the consequences of stroke in terms of body functions, activities and participation (17, 19). Following the ICF, we will discuss available literature and, subsequently, the design of an ongoing observational study into the time course and mechanisms underlying standing balance recovery. For this purpose, we distinguish between recovery of motor impairments of the most-affected lower limb (i.e., ICF level of body functions) and an improved ability to maintain standing balance as an integral part of daily life activities (i.e., ICF level of activities).

#### Time Course of Lower Limb Recovery

Unfortunately, only few longitudinal studies have been designed to investigate prospectively the time course of recovery of lower limb function (20–23) and activities (24–26) early after stroke. These studies suggest that recovery of motor impairments, such as synergy-dependency (20, 22, 23) and weakness (21, 23), mainly occurs in the first 5 weeks and levels off between 8 to 12 weeks poststroke (20–22). However, most survivors experience residual impairments in dissociating voluntary foot and leg movements from intra-limb synergies (27, 28) and muscle strength (23) which is associated with a decreased contribution of this leg to standing balance control (29–32). These early time-dependent changes remain poorly understood, but can be conceptualized as spontaneous neurological recovery as reflected by the passage of time (23).

Similar regularities in recovery patterns of activities involving the lower limbs have been shown. Likewise, most improvements in walking (6, 24–26) and other daily life activities (21, 23) were seen in the first weeks and regaining standing balance is found imperative to such recovery (6). One might suggest that spontaneous neurological recovery is associated with, if not determinant for these rapid improvements. This would mean that the ability to complete these tasks is restored with the same movement repertoire, or quality, the patient had before the stroke (i.e., behavioral restitution) (18, 19, 33). However, previous longitudinal research is largely limited to outcomes showing the mere accomplishment on these tasks. As these measures are unable to discriminate *how* the task is performed (19, 34, 35), little has been learned so far about the time course of recovery regarding qualitative aspects of movement when standing balance is restored.

#### Mechanisms Underlying Recovery of Standing Balance Control

As recently suggested (28), a number of severely affected subjects fail to show neurological recovery (28), leaving them entirely dependent on learning to use alternative ways to maintain their standing balance (i.e., behavioral compensation). However, even “well-recovered” patients with near normal clinical scores may show a disproportional reliance on the less-affected leg to balance control (31, 36). This is illustrated by more recent posturographic studies showing that bilateral COP displacements at the feet separately, as a reflection of the anticipatory modulation of ankle muscle activity aiming to minimize body sway (37, 38), are poorly synchronized (32, 39) and unequal (29–31, 40, 41) as compared to healthy controls. It seems that neurological recovery, even if occurring, is rarely complete and an even larger portion of survivors may depend on using compensation strategies to deal with residual impairments.

In favor of this notion, few longitudinal studies did show that standing balance improves in many patients *without* any concomitant improvements in anticipatory control of most-affected leg muscles in response to rapid arm movements (34, 42) or *without* restitution of symmetric exertion of corrective COP movements during unperturbed, quiet stance (2, 30, 40). However, these studies did unfortunately not start in the first weeks and assessed subjects at only few arbitrarily chosen time-points, leaving longitudinal associations with neurological recovery entirely underexplored.

As it remains unknown how stroke survivors “re-learn” to maintain standing balance in the early recovery phase when motor functions at the hemiplegic side improve, there is a need for early-started longitudinal research incorporating sensitive measures of task performance next to clinical scales. These studies may eventually progress our understanding of how spontaneous neurological recovery contributes to the re-acquisition of bipedal balance skills early after stroke onset.

### Objectives

In the current manuscript, we describe an observational cohort study that aims to prospectively investigate the time course of recovery of quiet stance balance control in the first 12 weeks after a first-ever hemispheric stroke. The relatively low functional demands of this condition (as compared to perturbed stance or walking) enables us to describe the process of balance skill re-acquisition even in more-severely impaired subjects and in the time window of spontaneous neurological recovery. Simultaneously, we will clinically observe the time course of recovery of lower limb motor impairments to investigate longitudinal associations with this leg's contribution to balance control.

The pre-defined research questions and hypotheses are:

What is the time course of recovery in the first 12 weeks poststroke in terms of balance control (a-)symmetries and overall stability during quiet stance? (i.e., project A).

First, we hypothesize that improvements in balance control symmetries toward values seen in healthy controls, as assessed through bilateral posturography (i.e., between-limb synchronization and contribution measures of corrective COP movements), are restricted to the first 5 weeks poststroke. Second, we hypothesize that an improved ability to maintain a stable standing position following traditional posturographic measures of body sway (i.e., stance stability) may develop beyond the time window and up until 12 weeks poststroke. As such, these later changes are hypothesized to reflect compensatory body stabilization exerted through the less-affected leg.

How are improvements in muscle synergies and ankle strength of the most-affected leg longitudinally associated with this leg's contribution to quiet stance balance control in the first 12 weeks poststroke? (i.e., project B).

First, we hypothesize that clinical improvements in muscle synergies (i.e., Fugl-Meyer Motor Assessment) and strength (i.e., Motricity Index) at the hemiplegic side are mainly seen within the first 5 weeks poststroke, in accordance with previous longitudinal studies investigating time-dependent change (20, 23). Second, we hypothesize to find within this time window longitudinal associations between recovery on these scales and improved between-limb symmetry in balance control. This means that clinically observed improvements in motor impairments relate over the first weeks to an improved ability of this leg to contribute to corrective COP movements while standing quietly.

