##### Quality of Task Performance

Quality of task performance is “defined through a direct comparison of a patient's motor execution of a task […] to able-bodied control subjects” (35). This means that the closer the movement matches those seen in controls, the better the quality. With regard to standing balance, quality of performance is best reflected by measures that establish the (a-)symmetry between the most- and less-affected side considering that healthy balance control is characterized by equal output generated through the legs in the form of corrective COP movements (39, 56, 57). For this purpose, synchronization and contribution measures will be calculated that show how well both limbs act together (32, 39, 56) and are equally involved (31, 57) in maintaining standing balance. As COP in the ML direction is less meaningful for bipedal balance control (56), we focus on the sagittal plane.

**Between-limb synchronization:** Between-limb synchronization is a measure of the temporal structure and similarity between bilateral COP (39, 56). For this purpose, the mean position is subtracted from left and right AP COP trajectories and, next, a cross-correlation at zero-phase leg on a frame-by-frame basis is calculated. This measure therefore shows how well COP displacements are alike, or synchronized.**Dynamic control asymmetry (DCA)**: DCA is a symmetry index of the root mean square (RMS) of the AP COP velocities for each leg separately (31, 57). A score of zero indicates equal contribution of both legs to balance control and positive or negative values indicating a relatively larger involvement of the less- or most-affected leg, respectively. We use the following equation: Symmetry index: 2x (RMS COP AP velocity *less-affected*- RMS COP AP velocity *most-affected*) / (RMS COP AP velocity *less-affected* + RMS COP AP velocity *most-affected*).

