##### Task Accomplishment

Metrics on task accomplishment are designed to show if a patient re-acquired the ability to complete the task irrespective of the underlying control strategy. With regard to standing balance, this is exemplified first by the level of independence following clinical scales and second by (traditional) posturographic measures of body sway that show how well a subject can stabilize their center-of-mass within the base of support. Therefore, these outcome variables will be used to address the process of regaining and optimizing the ability to maintain standing balance.

**Berg Balance Scale - standing unsupported item (BBS-s)**: The BBS-s assesses the ability to maintain assesses the ability to maintain a quiet standing posture without using the arms or support by another person. A score is assigned based on the level of independence needed to complete this task, where a score of 0 indicates no standing ability and a score varying between 1 and 4 indicate independent stance over 30 s to 2 min. The BBS has been reported to have excellent internal consistency as reported by a systematic review (58).**Stance stability**: To investigate overall stability when subjects attempt to stand quietly, we will calculate the root mean square (RMS) velocity of the net COP (i.e., combining two feet together without correction for feet orientation) in AP and ML direction. As the position of the net COP and the vertical representation of the body's center-of-mass correlate (59) these metrics reflect the ability to stand with minimal body sway.

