##### Project B

After describing the recovery time course, we aim to investigate longitudinal associations between motor impairments in terms of leg muscle synergies (i.e., FMA-LE) and ankle strength (i.e., ankle item of the MI-LE) serving as independent variables, and the DCA which is the dependent variable. First, we analyze the pattern of neurological recovery following these clinical scales by using similar methods as outlined above. Second, we will apply a recently discussed hybrid model (64) to investigate longitudinal associations over the first 12 weeks poststroke. This method has the advantage of disentangling the between- and within-subject effects of this relation.

The between-subjects covariate score is determined as the individual average value over time of the independent variables which reveals the association irrespective of the development over time. On the other hand, the within-subject covariate is calculated as the observed value at each time point minus the individual average (i.e., deviation score). By this, we can estimate whether longitudinal changes of the dependent and independent variables within a subject are associated, i.e., are increasing scores on the FMA-LE or MI-LE ankle item related to changes following the DCA. Similar covariates will be entered in the model and tested on significance.

For all statistical tests, the likelihood ratio test will be used to examine the need to enter random effects into the model and the Wald test will be used to obtain *P*-values for regression coefficients in the final model. A 2-tailed significance level of 0.05 will be used for all analyses.

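### The planned outcomes cannot attribute a change in balance control to one leg, so the leg-specific restitution and compensation readings need per-leg velocities beside the asymmetry index

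*Protocol article*

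**What the plan says.** All references are to the protocol article.

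- **Objectives, Project A.** Symmetry gains, measured by synchronization and contribution, "are restricted to the first 5 weeks poststroke". Stance stability may go on improving to week 12, and "these later changes are hypothesized to reflect compensatory body stabilization exerted through the less-affected leg".
- **Objectives, Project B.** An association between clinical recovery and symmetry is taken to mean an "improved ability of this leg to contribute to corrective COP movements while standing quietly".
- **Quality of Task Performance.** "DCA is a symmetry index of the root mean square (RMS) of the AP COP velocities for each leg separately". "A score of zero indicates equal contribution of both legs to balance control", and positive values mean relatively more involvement of the less-affected leg. For synchronization, "a cross-correlation at zero-phase leg on a frame-by-frame basis is calculated" from the two mean-centred anteroposterior (AP) signals.
- **Task Accomplishment.** Stance stability is the "root mean square (RMS) velocity of the net COP", both feet combined. The section says that metrics of this class show whether the task is achieved, whatever strategy the patient uses.
- **Project A and Project B (analysis).** Project A models each parameter over time. Project B relates the Fugl-Meyer leg score and the ankle item of the Motricity Index to one outcome, "and the DCA which is the dependent variable".

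The per-leg velocities enter the DCA equation. Neither Table 1 nor the analysis sections list them as outcomes, and Study Limitations does not raise the point.

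**The concern.** The study sets out to separate restitution of the most-affected leg from compensation by the less-affected leg. That requires knowing which leg changed. DCA improves if the most-affected leg becomes more active or if the less-affected leg becomes quieter, and its value does not say which. Stance stability carries no leg label. The article places it among metrics that do not depend on strategy, yet uses it to infer a strategy. The introduction criticises earlier longitudinal work for relying on measures that do not show how a task is performed.

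At stake is the leg-specific part of the conclusions. Clinical and Scientific Significance hopes that the results will help direct early training. A lower DCA caused by a quieter less-affected leg could be described as recovery of the most-affected leg. Stability gains shared by both legs could be described as compensation.

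**Working it through.** The plan states no figure to reproduce here; its DCA equation is evaluated directly.

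**Inputs.** L and M are the RMS AP COP velocities of the less- and most-affected leg. The equation comes from Quality of Task Performance. The article gives no velocities, so all values of L and M below are assumptions in arbitrary units.

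**Step 1: DCA depends only on the ratio.** With r = L/M,

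DCA = 2(L − M)/(L + M) = 2(r − 1)/(r + 1).

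Multiplying both legs by the same factor changes nothing.

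| State | L | M | DCA |
|---|---|---|---|
| Start | 12 | 6 | 2 × 6/18 = 0.667 |
| Most-affected leg rises | 12 | 8 | 2 × 4/20 = 0.400 |
| Less-affected leg falls | 9 | 6 | 2 × 3/15 = 0.400 |
| Both change | 10.5 | 7 | 2 × 3.5/17.5 = 0.400 |
| Both halve | 6 | 3 | 2 × 3/9 = 0.667 |
| Both fall, unequally | 7 | 5 | 2 × 2/12 = 0.333 |

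A DCA of 0.400 fixes r at (2 + 0.4)/(2 − 0.4) = 1.5 and nothing else. In the last row DCA improves although M is below its starting value. The numbers are illustrative, but the identity holds for any pairs with equal ratio.

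**Step 2: synchronization.** A correlation does not change when one signal is rescaled. If the less-affected leg only becomes quieter, synchronization stays where it was, so that route does not imitate better synchrony. A correlation also stays the same if the legs are exchanged, so it cannot say which leg changed. It is not a dependent variable in Project B.

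**Step 3: stance stability.** As a simplification, take net COP velocity as a load-weighted sum of the two legs. Assume a less-affected load share w of 0.6 and a between-leg correlation ρ of 0.5. Then

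net² = (wL)² + ((1 − w)M)² + 2ρ·wL·(1 − w)M.

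| State | L, M, w | DCA | Net velocity |
|---|---|---|---|
| Start | 12, 6, 0.6 | 0.667 | √(51.84 + 5.76 + 17.28) = 8.65 |
| Most-affected leg rises | 12, 8, 0.6 | 0.400 | √(51.84 + 10.24 + 23.04) = 9.23 |
| Less-affected leg falls | 9, 6, 0.6 | 0.400 | √(29.16 + 5.76 + 12.96) = 6.92 |
| Both fall in proportion | 9, 4.5, 0.6 | 0.667 | √(29.16 + 3.24 + 9.72) = 6.49 |
| Only load share shifts | 12, 6, 0.5 | 0.667 | √(36 + 9 + 18) = 7.94 |

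Simulated 30 s traces under the same inputs (200 runs) agree: net velocity 8.6, 9.3, 6.9, 6.5 and 7.9, with synchronization between 0.49 and 0.51 throughout.

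The last two rows show flat symmetry with better stability, the pattern that Objectives would read as compensation through the less-affected leg. Here it arises because both legs quieten equally or because only loading shifts. If DCA is flat, L/M is constant, so a stability gain does not by itself point to the less-affected leg.

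**Step 4: what separates the cases.** The pairs (12, 8) and (9, 6) show at once which leg moved, and both values are already needed to compute DCA.

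**The case against.** **Relative contribution is the declared construct.** The abstract's objective and the description of DCA are both worded in relative terms, and 12/8 and 9/6 have the same relative contribution. This stands: DCA measures that objective and should stay. The mismatch lies in the step to statements about one leg.

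**Project A has a second symmetry measure.** This stands as far as it goes. A quieter less-affected leg would move DCA without synchronization, which guards against one misreading. It still does not name the leg.

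**Project B's predictors belong to the most-affected leg, and the hybrid model isolates within-subject association.** This is outside evidence in favour of the intended reading. The outcome nevertheless remains a ratio.

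**DCA and net velocity read together partly separate the routes.** In the working, net velocity is 9.23 in one case and 6.92 in the other. That reading needs the load share, and no joint analysis is described.

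**A condensed article leaves detail to an analysis plan.** True in general. Here the article itself fixes the outcomes, Project B's dependent variable and the interpretation.

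Three stronger readings are tempting, and the article does not support them:

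- A reader might infer that compensation will be declared when stability is significant and symmetry is not. No such rule is stated; the compensation reading is worded as a hypothesis.
- A reader might infer that falling sway makes a quieter less-affected leg the expected route. It does not: both legs may fall in proportion. Selective quietening after week 5 would lower DCA when the first hypothesis has symmetry gains already over.
- A reader might infer that the clinical message will be reversed. That is possible but not shown, and the article words its clinical implications cautiously.

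**Conclusion.** The point holds in a limited form. DCA cannot distinguish a more active most-affected leg from a quieter less-affected one. Synchronization treats the legs alike, and stance stability pools them. The two leg-specific readings in Objectives are therefore not supported by the planned outcomes alone.

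The DCA result rests only on the stated equation. The net-velocity figures rest on assumed velocities, load share and correlation; they show that the ambiguity can arise, not how often it will. The conclusions on relative contribution are untouched. This is a cheap improvement worth making, not a fault that invalidates the design.

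**What to change.** 1. Keep DCA as the outcome for relative contribution.
2. Add log RMS AP COP velocity of each leg as secondary outcomes. In Project A, model leg by time and show control values per device. In Project B, use the two as additional dependent variables. On the log scale log L − log M = log r, which determines DCA. The leg-by-time term thus addresses relative contribution, and the per-leg trajectories show which leg moved.
3. Make a restitution or compensation statement about a leg only where these trajectories support it. Otherwise word the conclusion as a change in relative contribution.
4. Do not test compensation by correlating stance stability with the less-affected leg's velocity. Net COP contains that leg's COP, so the two are coupled by construction. In the working, net velocity falls with L from 12 to 9 both when M stays at 6 (6.92) and when M falls in proportion (6.49).

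**Cost.** No new measurement, and two more secondary outcomes to report. Ten controls give an imprecise benchmark, more so if they are divided between devices, although the trajectories themselves do not depend on it. Per-leg velocities are absolute and not normalised for overall sway, so they should be read beside DCA and with the equipment covariate already planned.
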